### Statistical analysis and sample size calculation

3.15

Standard descriptive statistics will be used to analyze baseline participant characteristics. We will produce summary statistics such as means, medians, standard deviations, and ranges for measured variables. We will tabulate frequencies for categorical and ordinal variables. We will use graphical methods extensively to examine distributions, identify potentially influential points, and guide data transformations if warranted. For continuous variables with markedly non-normal or skewed distributions, appropriate transformation may be required, such as natural logarithms, which we will apply as necessary and appropriate.^[43]^ In the sections below, we will assume, when discussing particular outcomes, that the appropriately transformed variables will be used. We will perform analysis according to the intention-to-treat (ITT) principle (i.e., subjects will be analyzed according to the treatment group to which they will be randomly allocated regardless of drop-out).

To determine the effects of ILM on fatigue, we will use mixed effects models.^[44]^ This statistical procedure takes into account within-subject correlations from repeated measurements in the same subjects and allows estimation of between-group difference without necessitating that the last observation is carried forward or exclusion of participants with missing data. Tests of ITT differences between intervention arms with respect to change in BFI-C will be based on time-intervention interactions in the mixed-effects models. Although randomization theoretically balances the potential confounders between treatment groups, occasional unequal distribution can be seen. Should this happen, the effect of confounding will be evaluated by including the potential confounders as co-variates in the models.^[43]^ For secondary outcomes, we will use similar analytical strategies for co-morbid symptoms. To evaluate the long-term durability of treatment effect, we will display long-term data descriptively. It is possible that the long-term outcome may display different patterns from short-term therapeutic effect. If this occurs, we may need to create piece-wise linear mixed-effects models to fit the data and test for statistical significance on outcome change among treatment groups.

We have based our sample size calculation on our preliminary study. We plan to enroll and randomize 140 participants (2:2:1) to ILM, SILM, and WLC. Assuming a 20% attrition rate, we will have 45 participants in each of the ILM and SILM groups and 22 participants in the WLC group who will provide evaluable outcomes. In our previous study, we found that ILM produced a greater reduction in BFI-C intensity at the end of intervention (Week 4 from baseline) at a magnitude of 0.60 SD (Standard Deviation) as compared to SILM. Given an alpha of 5%, with 45 subjects in each of the ILM and SILM groups, we will be able to detect a between-group difference of reduction in BFI-C of 0.60 SD with 80% power. With 45 subjects each in the ILM and SILM groups and 22 participants in the WLC group, a power of 80% and two-sided alpha of 0.05, we will be able to detect an effect size of 0.71 SD (i.e., difference of reduction in BFI-C) between ILM and WLC or SILM and WLC groups. This is a conservative way to estimate sample size since the longitudinal analysis using all repeated measures with the mixed-effects model specified in the analysis plan will provide higher power than a *t* test.

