## Specific aims and hypotheses

2

Our primary specific aim is to evaluate the efficacy of infrared laser moxibustion on CRF in BCS. We hypothesize that the Infrared Laser Moxibustion (ILM) group will have significantly greater improvement in the fatigue score from Baseline to Week 6 (primary end point) to Week 18 (follow up) compared to sham ILM (SILM) and waitlist control (WLC) groups. The primary outcome measure is the change over time in the mean score of the Chinese version of the Brief Fatigue Inventory (BFI-C).

Our secondary aim is to evaluate the efficacy of infrared laser moxibustion in insomnia, anxiety, depression, and pain among BCS experiencing CRF. We hypothesize that BCS with CRF randomized to ILM will have significantly greater improvement in insomnia, anxiety, depression, pain, and quality of life from Baseline to Week 6 and from Baseline to Week 18 compared to those randomized to SILM and WLC. Secondary outcome measures include the change over time in the mean score of the Chinese versions of the Pittsburgh Sleep Quality Index (PSQI), Hospital Anxiety and Depression Scale (HADS), Brief Pain Inventory (BPI), and Functional Assessment of Cancer Therapy-Breast (FACT-B).

Our exploratory mechanistic aim is to explore the effects of infrared laser moxibustion on telomere length among BCS with CRF. We hypothesize that BCS with CRF who are randomized to ILM will have a significantly greater increase in telomere length over time from Baseline compared to SILM and WLC.

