### Outcome measures

3.7

Outcome measures and data collection time points are listed in Table 2. The primary endpoint of this study is the post-intervention assessment (T2, after 6 weeks of treatment sessions). We will measure primary and secondary outcomes at baseline (T0), mid-intervention (T1, after 3 weeks of treatment sessions), post-intervention (T2) and at follow-up (T3 and T4, 6, and 12 weeks after 6 weeks of treatment sessions). The collected clinical data will be collected with REDCap.

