#### Primary Outcome

3.7.1

Our primary outcome is the fatigue score measured by the Chinese version of the Brief Fatigue Inventory (BFI-C).^[30,31]^ The scale score has excellent internal consistency of 0.96. The indicators of the scale assessment include the current level of fatigue; the fatigue level within the past 24 hours; and the impact of CRF on physical activities, emotions, ability to walk, ability to work, relationships with others, and enjoyment of life within the past 24 hours. The BFI-C uses 10-point numeric descriptions: scores of 1 to 3 represent mild levels of fatigue, scores of 4 to 6 represent moderate levels of fatigue, and scores of 7 to 10 represent severe levels of fatigue. The endpoint is the change in fatigue score from Baseline to Week 6 (end of treatment) among the 3 groups.

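### The stated primary test, a time-by-intervention interaction, is not tied to Week 6 or to the ILM-SILM comparison that was powered

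*Protocol article*

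**What the plan says.** Sections 3.7 and 3.7.1 of the protocol article fix the endpoint at Week 6: "The primary endpoint of this study is the post-intervention assessment (T2, after 6 weeks of treatment sessions" and "The endpoint is the change in fatigue score from Baseline to Week 6 (end of treatment) among the 3 groups". Section 3.15 powers ILM against SILM as a two-group comparison of reduction in BFI-C: 0.60 SD, 45 evaluable per arm, 80% power.

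The test is given once, in section 3.15: "Tests of ITT differences between intervention arms with respect to change in BFI-C will be based on time-intervention interactions in the mixed-effects models". Four other statements bear on which data and which model that means:

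- Section 3.7 lists the visits: "We will measure primary and secondary outcomes at baseline (T0), mid-intervention (T1, after 3 weeks of treatment sessions), post-intervention (T2) and at follow-up", the follow-up visits being Weeks 12 and 18. Section 3.1 omits Week 3.
- Section 3.15 argues that the sample size is conservative because "the longitudinal analysis using all repeated measures with the mixed-effects model specified in the analysis plan will provide higher power" than a t test.
- Section 2 states the primary hypothesis as improvement "from Baseline to Week 6 (primary end point) to Week 18 (follow up) compared to sham ILM (SILM) and waitlist control (WLC) groups".
- Section 3.15 says long-term data will be displayed descriptively, but adds that if the later pattern differs "we may need to create piece-wise linear mixed-effects models to fit the data" and test for significance among the groups.

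**The concern.** An interaction between time and arm is a family of quantities. With visit categorical and SILM as reference, one member (ILM by Week 6) is exactly the endpoint. Other members are not:

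- A linear-time interaction over all visits compares 18-week slopes, and 12 of those 18 weeks are off treatment. An effect that is real at Week 6 and then fades bends the line back towards zero.
- A joint test across three arms asks whether any arm differs from any other at any visit. A non-specific benefit shared by ILM and SILM but absent in WLC can make it significant, although the trial's aim is specific efficacy.
- A joint ILM-SILM test over all visits can be significant because of a difference that appears only after Week 6.

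The text does not choose among these. It also lets the longitudinal model change form once the later pattern has been seen. At stake is whether the trial's main conclusion answers the question it was sized for.

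**Working it through.** **The plan's own figure.** Inputs from section 3.15: 45 per arm, 0.60 SD of change, two-sided 5%. The standard error of the difference is √(2/45) = 0.2108, so z = 0.60/0.2108 = 2.846 and power = Φ(2.846 − 1.960) = 81.2%. The exact t calculation gives 80.4%. The stated 80% is reproduced, and it belongs to a two-group comparison of change.

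**Assumptions for the rest.** Visits at Weeks 0, 3, 6, 12 and 18; complete data on 45/45/22; compound symmetry; effects in units of the SD of change, positive favouring ILM. The within-visit residual variance is then 0.5 and the correlation drops out. The trajectories are assumed; the protocol gives none.

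**Linear slope over Weeks 0-18.** Mean time is 7.8, so the centred times are −7.8, −4.8, −1.8, 4.2, 10.2, with sum of squares 208.8. The standard error of the ILM-SILM slope difference is √(0.5/208.8 × 2/45) = 0.01032. The slope is Σ(centred time × effect)/208.8, and the implied Week 6 difference is 6 × slope.

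- Sustained: 6.12/208.8 = 0.0293, z = 2.84.
- Half lost: 2.43/208.8 = 0.0116, z = 1.13.
- All lost by Week 18: −1.26/208.8 = −0.0060, z = −0.58.
- Gone by Week 12: −2.52/208.8 = −0.0121, z = −1.17.

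**Joint categorical test, ILM-SILM (4 df).** The changes from baseline have variance 1 and covariance 0.5, with inverse 2I − 0.4J. The noncentrality is 22.5 × [2Σd² − 0.4(Σd)²]. For all lost this is 22.5 × (1.08 − 0.576) = 11.34; for half lost, 22.5 × (1.485 − 1.089) = 8.91. The three-arm version has 8 df, with SILM = WLC here.

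| ILM − SILM at Weeks 3, 6, 12, 18 | Week 6 contrast | Slope 0-18, 1 df | Week 6 difference implied by slope | Joint 4 df / 8 df |
|---|---|---|---|---|
| 0.30, 0.60, 0.60, 0.60 (sustained) | 81% | 81% | 0.18 | 83.6% / 81.5% |
| 0.30, 0.60, 0.45, 0.30 (half lost) | 81% | 20% | 0.07 | 65.8% / 62.1% |
| 0.30, 0.60, 0.30, 0 (all lost by Week 18) | 81% | 9% | −0.04 | 77.7% / 74.9% |
| 0.30, 0.60, 0, 0 (gone by Week 12) | 81% | 22% | −0.07 | 83.6% / 81.5% |

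In the third row, 8.5 of the 9 points are rejections in the wrong direction: Φ(0.585 − 1.960) = 0.085. A linear model that stops at Week 6 keeps 81%.

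**No ILM-SILM difference.** Let both beat WLC by 0.355 SD at Week 3 and by 0.71 SD (the WLC effect size in section 3.15) from Week 6 on. The weight is 90 × 22/112 = 17.68 and the quadratic form is 2 × 1.638 − 0.4 × 6.175 = 0.807, so the noncentrality is 14.26. The 8-df three-arm test rejects in 77% of trials, and the 2-df linear version also in 77%. Restricting the three-arm test to Weeks 0-6 does not cure this: 66% (categorical) or 77% (linear). A pairwise ILM-SILM test stays at 5%.

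**Difference only after Week 6.** With ILM − SILM of 0, 0, 0.30 and 0.60 at Weeks 3, 6, 12 and 18, the ILM-SILM interaction over all visits rejects in 84% (4 df) or 93% (slope), against 5% for the Week 6 contrast.

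**The case against.** A reader might infer that the primary test is an interaction over every visit to Week 18 and is therefore not the Week 6 ILM-SILM difference. The document does not say that. It defines the change of interest as Baseline to Week 6, says long-term data will be shown descriptively, and refers to tests in the plural between intervention arms; the power section is pairwise. An ILM-by-Week 6 term against SILM is itself a time-by-intervention interaction. No three-arm omnibus test is named, and the piece-wise sentence concerns long-term patterns, so it does not establish that a single straight line is the default. All of this stands.

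The severe loss of power also needs a particular combination: linear time to Week 18 and a fading effect. Fading is the case in which section 3.15 allows the line to be replaced. That switch rests on the observed pattern, however, so it does not fix the primary test in advance.

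A reader might also conclude that the claim of higher power should be struck out. The calculation above uses complete cases, so it cannot show that. Take 56 randomized per arm, with 45 complete, 5 lost after Week 3 and 6 lost after baseline, and correlation 0.3 to 0.7 (all assumed except the 56 and the 45). The Week 6 contrast from the mixed model then has 83-84% power, or 88-94% if baseline means are constrained equal. A gain is plausible for that contrast.

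Finally, a separate analysis plan may settle covariance structure and coding, and leaving those details to it is no fault. What remains is that this document states a test, and a power argument built on it, that do not select the quantity defined as primary.

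**Conclusion.** The point holds as a failure to tie the test to the endpoint; it does not hold as proof that the wrong test has been chosen. Section 2 and the all-repeated-measures argument in section 3.15 pull Week 18 into the inference, the descriptive display in section 3.15 pushes it out, and neither visit nor arm pair is named for the test.

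The consequence depends on the reading. It is serious for a 0-18 week slope with a fading effect (power 9-22% against 81%) and for a three-arm joint test when ILM equals SILM (about 77% rejection). It is smaller for a categorical joint test: about 75-84% when the effect is sustained, gone by Week 12 or gone by Week 18, and 62-66% when half is lost. It is nil if the ILM-by-Week 6 term against SILM is what is meant. The figures rest on compound symmetry, complete data and the assumed trajectories. A power gain over the t test is not assured under a slope or joint test.

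**What to change.** In section 3.15, state that the mixed model has visit as a categorical factor and that the primary test is the single-df contrast ILM minus SILM in BFI-C change from Baseline to Week 6. Estimate ILM minus WLC at Week 6 from the same model. Make Weeks 12 and 18 secondary, and reword section 2 to match. Any piece-wise model should then be a secondary description that cannot replace the primary test.

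Keep the sentence on higher power, but at most qualify it as referring to the Week 6 contrast from this model.

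The cost is a few sentences. The contrast keeps the stated power (81.2% normal, 80.4% t, at 0.60 SD with 45 per arm) and a 5% rejection rate when ILM equals SILM at Week 6, whatever WLC or later visits show. No change in sample size and no new data are needed.

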### Randomization and allocation concealment

3.4

We will randomize participants to ILM, SILM, or WLC groups with an allocation ratio of 2:2:1. The biostatistician will conduct allocation using permuted block randomization with varying block sizes, stratified by age (<50/≥50 years of age) and baseline fatigue level (<7/≥7). The randomization sequence generation will be completed prior to the recruitment of participants and the investigators will remain blinded to the treatment condition. Randomization information will be sealed in opaque envelopes that we will open after participants complete their baseline assessment.

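### The covariates and outcome scale of the primary analysis are left to be settled after the data are seen; fixing baseline BFI-C, the strata and the scale in advance is a free improvement

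*Protocol article*

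**What the plan says.** All references are to the protocol article.

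- **Primary test (3.15).** "Tests of ITT differences between intervention arms with respect to change in BFI-C will be based on time-intervention interactions in the mixed-effects models".
- **Covariates (3.15).** The trigger is an observed imbalance: "Although randomization theoretically balances the potential confounders between treatment groups, occasional unequal distribution can be seen". The consequence follows: "Should this happen, the effect of confounding will be evaluated by including the potential confounders as co-variates in the models". No candidates, threshold or primary model are named.
- **Transformation (3.15).** Graphs are to guide transformations, with natural logarithms as the example for markedly skewed variables. The section continues: "we will assume, when discussing particular outcomes, that the appropriately transformed variables will be used". BFI-C is not exempted.
- **Stratification (3.4).** Randomisation is "stratified by age (<50/≥50 years of age) and baseline fatigue level (<7/≥7"). The covariate strategy in 3.15 names neither factor.
- **Baseline as a measured occasion (3.7).** "We will measure primary and secondary outcomes at baseline (T0), mid-intervention (T1, after 3 weeks of treatment sessions), post-intervention (T2"), followed by T3 and T4.
- **Endpoint and power (3.7.1, 3.15).** Both are stated as a difference in BFI-C change. Power is computed as a t test, and the mixed model is said to give more.

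**The concern.** Two features of the primary result are left open until the data are in hand: which covariates are in the model, and on what scale BFI-C is analysed. If arms look unequal on some characteristic, there will be an unadjusted and an adjusted estimate, and the article does not say which one answers the primary question. If BFI-C looks skewed and is logged, the model estimates something other than the difference in BFI-C change on which the endpoint and the power are stated.

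The rule is also aimed at the wrong variables. Age stratum and baseline fatigue are the factors already chosen as important enough to stratify on. Stratification keeps them close to balanced, so a rule triggered by imbalance is least likely to bring them in. Leaving prognostic strata out usually makes standard errors too large, which is conservative but wasteful.

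Last, a time-by-arm interaction with T0 as a free response does not by itself use the baseline as efficiently as conditioning on it.

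**Working it through.** **Inputs from the article.** 140 randomised 2:2:1 gives 56, 56 and 28. With 20% attrition, 56 × 0.8 = 44.8, stated as 45 per laser arm. Effect 0.60 SD of the reduction in BFI-C; alpha 5%, taken as two-sided.

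**Assumed, because the documents do not give them.** The correlation r between baseline and Week 6 BFI-C (0.3 to 0.7), and the ratio k of the baseline SD to the Week 6 SD (0.6 to 1). The 0.60 SD is read as SDs of change, and time as categorical.

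**1. The stated power.** With 45 per arm and 0.60 SD, the noncentral t gives 80.4% (normal approximation 81.2%). The 80% reproduces with no covariate.

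**2. Free T0 response against constrained baseline.** Set the Week 6 and baseline SDs to 1, with complete data at T0, T1 and T2 and compound symmetry. The variance of the Week 6 contrast is:

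- baseline means free: 2 × 2(1 − r)/45. At r = 0.5 this is 0.0444, the same as a change-score comparison, so power stays at 81.2% (normal);
- baseline means constrained equal, equivalent here to ANCOVA: 2(1 − r²)/45. At r = 0.5 this is 0.0333, with power 90.8% (normal).

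In the free case with complete data, the higher power that 3.15 expects over a t test does not appear.

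**3. Size of the possible gain.** With Week 6 SD 1 and baseline SD k, Var(change) = 1 + k² − 2rk and Var(ANCOVA) = 1 − r². The ratio is (1 − r²)/(1 + k² − 2rk), which is (1 + r)/2 at k = 1 and exactly 1 when k = r. Power at 0.60/√ratio, noncentral t, 45 per arm (unadjusted 80.4%):

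| k | r = 0.3 | r = 0.5 | r = 0.7 |
|---|---|---|---|
| 1.0 | 93.7% | 90.2% | 86.3% |
| 0.8 | 88.8% | 84.6% | 81.1% |
| 0.7 | 86.3% | 82.4% | 80.4% |
| 0.6 | 83.9% | 80.9% | 81.1% |

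Values of k below 1 are plausible because entry requires fatigue of at least 4 (3.1, 3.2), which restricts the spread at baseline.

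**4. How often the trigger fires.** If imbalance meant p < 0.05, which the article does not say, then with m independent candidates the chance of at least one is 1 − 0.95^m: 22.6% for m = 5 and 33.7% for m = 8.

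**5. Type I error.** Simulation used 10,000 null trials per scenario, 45 against 45, with 1 to 8 covariates and assumed joint R² of 0.10 to 0.25. A mechanical rule that adjusts for every covariate with imbalance p < 0.05 gave 4.3% to 4.8%. Taking the smallest p-value among the unadjusted, single-covariate and fully adjusted models gave 7.4% to 10.6%.

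**The case against.** The strongest reply is that this is a condensed article. Section 3.15 itself refers to a model specified in an analysis plan, which is not shown and may fix the covariates. That answers any complaint resting only on silence, so one cannot conclude that the strata are absent from the final model. It does not answer the rule the article does state, which is triggered by imbalance and leaves the primary result undesignated. If the unseen plan fixes the covariates, 3.15 needs to agree with it.

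Four stronger readings are tempting, and the documents do not support them:

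- **Baseline BFI-C is left out.** T0 is a measured occasion and the test concerns change, so baseline can be in the model. If baseline means are constrained equal, the gain is already obtained. The article does not say.
- **The adjusted model replaces the primary one.** The text says the effect of confounding will be evaluated, which can be read as a supplementary check. The ambiguity is the defect.
- **The rule inflates type I error.** Applied mechanically, it does not (step 5). Inflation needs someone to select the best result, which the article does not propose. It merely fails to rule that out.
- **A log fails because BFI-C can be 0.** Section 3.7.1 gives bands from 1 to 10, and the 0 to 10 scale in 3.2 belongs to the screening item. The objection to a log is the change of estimand.

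The claim of higher power also keeps some force outside the complete-data case, since a mixed model can use participants who miss Week 6.

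**Conclusion.** The point holds as a free improvement. Section 3.15 states a covariate rule with no list, threshold or designated primary result, and a transformation rule that can reach the primary outcome, whose endpoint and power are stated as a difference in BFI-C change.

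A reader might infer that the trial is underpowered. It is not on this account: the planned 80% for ILM against SILM is met without adjustment. The cost is possible forgone precision of uncertain size. It ranges from about 13 points of power (80.4% to 93.7% at r = 0.3 with equal SDs) to none (k = r = 0.7). It arises only if baseline means are not constrained. Both r and k are assumptions; the upper figures need equal SDs at baseline and Week 6.

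**What to change.** Replace the imbalance and transformation rules for the primary analysis with a few sentences to this effect:

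- The primary mixed model always includes baseline BFI-C, either as a continuous covariate with its interaction with visit or by constraining baseline means to be equal across arms.
- It always includes the age stratum. The fatigue stratum is covered by continuous baseline BFI-C or added as a factor.
- This model gives the primary result whatever balance is observed. Adjustment for other characteristics found unequal is a labelled sensitivity analysis.
- BFI-C is analysed untransformed in the primary analysis.

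If the analysis plan already says this, bring 3.15 into line with it. The cost is drafting only: both stratification factors and baseline BFI-C are already collected, and nothing changes for participants or the sample size. The wording should be fixed before unblinded data are seen.

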### Study design

3.1

We will conduct a randomized controlled, 3-arm trial of ILM compared to SILM and WLC for moderate (score of 4–6 on BFI-C) to severe (score of 7–10) fatigue in BCS. After random assignment to 3 groups, patients in the ILM and SILM groups will receive 20-minute treatments of real/sham infrared laser moxibustion twice per week for six weeks. We will have a 12-week follow-up period to evaluate the durability of the treatment effects. We will assess patient-reported fatigue and other comorbid symptoms at Baseline, Weeks, 6, 12, and 18, respectively. We have included details of the study timeline in Figure 1. This study was approved by the Institutional Review Board of Yueyang Hospital and registered with the identifier NCT03553355 (12 June 2018) at ClinicalTrials.gov. All participants will provide written informed consent.

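### The hypotheses claim significant superiority to Week 18, but the analysis names no unconditional Week 18 contrast and offers a long-term test only if the observed pattern looks different

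*Protocol article*

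**What the plan says.** **Hypotheses.** Section 2 of the protocol article expects ILM to show "significantly greater improvement in the fatigue score from Baseline to Week 6 (primary end point) to Week 18 (follow up" visit, relative to both SILM and WLC. For insomnia, anxiety, depression, pain and quality of life it expects significantly greater improvement "from Baseline to Week 6 and from Baseline to Week 18 compared to those randomized to SILM and WLC".

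**Purpose of follow-up.** Section 3.1 states: "We will have a 12-week follow-up period to evaluate the durability of the treatment effects".

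**Primary endpoint.** Section 3.7.1 limits this to the end of treatment: "The endpoint is the change in fatigue score from Baseline to Week 6 (end of treatment) among the 3 groups".

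**Analysis.** Section 3.15 says that tests of change in the fatigue score (BFI-C) "will be based on time-intervention interactions in the mixed-effects models", with a similar approach for secondary outcomes. It does not say which visits enter the test or whether time is categorical or linear. On durability it says: "To evaluate the long-term durability of treatment effect, we will display long-term data descriptively". It continues: "It is possible that the long-term outcome may display different patterns from short-term therapeutic effect". And then: "If this occurs, we may need to create piece-wise linear mixed-effects models to fit the data and test for statistical significance".

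**The concern.** A hypothesis of significant superiority at Week 18 cannot be answered by a descriptive display, and the only long-term test mentioned is optional and depends on how the data look.

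The trigger also points the wrong way. If the Week 6 benefit is maintained, as Section 2 predicts, the long-term pattern does not differ from the short-term one and no test is called for. If the pattern does differ, the same curves decide that a test is run and what model it uses. Its p-value would not then have its nominal meaning.

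At stake is the durability claim, which is the stated reason for 12 weeks of follow-up.

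**Working it through.** **1. The texts side by side**

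| Question | Section 2 | Section 3.15 |
|---|---|---|
| Claim or analysis at Week 18 | Significantly greater improvement with ILM | Descriptive display |
| Comparators | SILM and WLC | No Week 18 contrast named |
| When tested | Implied in all cases | Optionally, if the pattern differs |
| Criterion for differing; knot | – | Not given |

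**2. The plan's own power figure**

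Inputs from Section 3.15: 140 randomised 2:2:1 (56:56:28), 20% attrition, 0.60 SD, alpha 5% (taken as two-sided).

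- Evaluable: 56 × 0.8 = 44.8 and 28 × 0.8 = 22.4, matching the stated 45, 45 and 22.
- Normal approximation for 45 v 45: power = Φ(0.60/√(2/45) − 1.960) = Φ(2.846 − 1.960) = Φ(0.886) = 81.2%.
- Two-sample t-test: 80.4%.

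The stated 80% reproduces. The 0.60 SD is a pilot effect at the end of intervention (Week 4), not a follow-up effect.

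**3. An unconditional Week 18 ILM minus SILM contrast** (t-test, 45 per arm, two-sided 5%)

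| Week 18 effect | Power |
|---|---|
| 0.60 SD (full effect persists) | 80.4% |
| 0.45 SD (assumed) | 56.0% |
| 0.30 SD (assumed) | 29.1% |

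The article gives no Week 18 effect. These figures also assume that 45 per arm are still evaluable at Week 18; the 20% attrition is not tied to a visit.

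**4. What a conditional rule could do**

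The trigger is undefined, so one was assumed: test Week 18 only if the ILM–SILM difference at Week 18 departs from that at Week 6 by more than 0.2 or 0.3 SD in either direction. The correlation ρ between Week 6 and Week 18 change was assumed to be 0.3 to 0.7. There were 20,000 simulated trials per row, 45 per arm, with a t-test at Week 18.

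| ρ | Trigger (SD) | 0.60 SD persists: test run | Run and significant | Significant if always tested | No effect: overall false positives | No effect: false positives among tests run |
|---|---|---|---|---|---|---|
| 0.3 | 0.2 | 42.3% | 31.8% | 80.4% | 3.8% | 9.0% |
| 0.3 | 0.3 | 23.3% | 16.5% | 80.0% | 2.9% | 12.9% |
| 0.5 | 0.2 | 34.2% | 25.9% | 80.2% | 3.0% | 8.9% |
| 0.5 | 0.3 | 15.4% | 11.2% | 80.9% | 1.9% | 12.3% |
| 0.7 | 0.2 | 22.0% | 16.6% | 80.2% | 1.8% | 8.3% |
| 0.7 | 0.3 | 6.5% | 4.9% | 80.5% | 0.6% | 10.3% |

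Check of one trigger rate: the change in the between-arm difference has SD √(4(1−ρ)/45). At ρ = 0.5 this is 0.211, so P(|change| > 0.2) = 2(1 − Φ(0.949)) = 34.3%, against 34.2% simulated.

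If instead a 0.60 SD effect at Week 6 has vanished by Week 18, the test runs in 89–99% of trials and the false-positive rate among tests run is 3.8–5.0%. The distortion of the p-value therefore depends on the true pattern. It shows here when there is no effect at either time.

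**The case against.** The strongest reply is that a Week 18 test may already exist. The mixed model tests time-by-intervention interactions, the sample-size paragraph of Section 3.15 says the longitudinal analysis draws on all repeated measures, and Section 3.7 runs visits to 12 weeks after treatment. A reader who infers that Week 18 is wholly untested, with zero power, goes further than the text allows. What remains is that the article does not say Week 18 enters the confirmatory test, while its one sentence about durability assigns the long-term data to description. An interaction across several visits is also not a Week 18 comparison, since it can be significant because of Week 6 alone.

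A reader might also infer a false-positive rate near 10%, from 1 − 0.95² = 9.75% for a choice between two tests. The documents do not support this. The two tests would use the same patients and visits and so would not be independent, and the plan does not say that either may be picked. In the simulation the overall rate stayed at 0.6–3.8%. The simulation models a triggered Week 18 t-test and not the piece-wise model itself, so it does not bound every form of data-driven modelling.

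Finally, an analysis plan not shown may say more. It could add a Week 18 test only by departing from the explicit descriptive sentence, so the conflict lies in this document.

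**Conclusion.** The point holds as a conflict between the stated hypotheses and the stated analysis. No unconditional Week 18 contrast is named, the conditional test has no criterion and no knot, and the hypothesised sustained effect is the case that would not trigger it.

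Under the assumed triggers and correlations, the chance of a significant Week 18 result when 0.60 SD persists falls from about 80% to about 5–32%. With no effect at either time, about 8–13% of the tests actually run are falsely positive. No inflation of the overall error rate is claimed.

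Nor should 80% power be read across to Week 18 without the condition that the full end-of-treatment effect persists. The Week 6 primary endpoint and its conclusion are unaffected. Perceived stress, although measured, is not among the outcomes named in the Section 2 hypotheses.

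**What to change.** **Preferred.** In Section 3.15, replace the descriptive and conditional piece-wise text with the following:

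- From the mixed model, with time as a categorical visit, estimate the ILM minus SILM contrast in BFI-C change from baseline to Week 18 and report it with a 95% CI whatever the curves show.
- Test it at two-sided 5% only after the Week 6 comparison succeeds.
- Report the Week 12 contrasts, the WLC contrasts and the secondary-outcome Week 18 contrasts as estimates with 95% CIs. Use plots as support.
- Reword Section 2 so that significance is claimed only for contrasts that are tested.

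**Alternative.** Reword all Week 18 hypotheses in Section 2 as descriptive and drop the conditional test. This removes the conflict equally well if the investigators do not want a formal durability claim.

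**Cost.** Either change is wording only, since Weeks 12 and 18 are already collected. It should be made before long-term results are seen by arm. The ordered test has a price: with 0.60 SD at both times, the chance that both succeed lies between 2 × 80.4% − 100% = 60.8% and 80.4%, depending on the correlation, and it is lower if the effect fades. That is a reason to report the interval in every case.
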